### Additional consent provisions for collection and use of participant data and biological specimens {26b}

The blood test and magnetic resonance spectroscopy (MRS) are optional measures. The request for blood sample collection is covered in the original informed consent procedure and an additional informed consent is provided to participants who are willing and eligible for the MRS measure.

## Interventions

### Explanation for the choice of comparators {6b}

Although both PL and tES have shown beneficial effects in restoring visual functions in patients with glaucoma, it is still unclear whether a combined approach can offer greater benefits than monotherapy. Therefore, our goal is to compare the effectiveness of combined PL and tES with monotherapy in improving the visual field in glaucoma patients. Through this comparative study, we aim to understand the potential combined effects and identify the optimal approach for enhancing visual rehabilitation in glaucoma patients.

### Intervention description {11a}

The intervention comprises of PL and tES. Depending on the group they are assigned to, participants receive one of the different combinations of perceptual training and stimulation. The eye with the least visual field defect will be chosen as the training eye, a choice made to maximize the potential benefits of the training intervention in the patients’ daily lives. In the rare instances when the visual field defects are identical in both eyes, the eye with higher visual acuity is chosen as the training eye.

For PL, a customized computer-based program specifically designed for vision restoration training will be utilized. The selection of a region of interest (ROI) is a crucial step, which is based on neighborhood weighting and eccentricity factors derived from the baseline visual field of high-resolution perimetry (HRP). To mitigate random responses observed during HRP testing, a neighborhood weighting rule is applied, where the accuracy value of each point is replaced by the average value of its surrounding 20 points. Additionally, the weighting of points is influenced by their eccentricity, giving higher importance to central points compared to peripheral ones. This process generates a map with varying accuracy scales, from which the 40 most promising training points are selected within the ROI. Within this ROI, a Gabor discrimination task is employed as the training task, with the training difficulty adjusted through contrast variations (initially set at 0.8 and ending at 0.1). The Gabor size is m-scaled according to eccentricity, and two Gabor orientations (horizontal or vertical) are presented to the training positions of the training eye monocularly.

In the real PL group, 80% of the training positions are selected from the ROI, while the remaining 20% are selected from the central 5-degree region. Conversely, in the placebo PL group, 80% of the training positions are chosen from the central 5-degree area, and the remaining 20% are selected from the ROI.

A 1-up and 1-down session-by-session staircase strategy is used for each session. If the accuracy of a given position falls within the 75 to 85% range, the contrast remains the same for subsequent training sessions. If the accuracy drops below 75%, the difficulty is decreased by increasing the contrast in increments of 0.1. Conversely, if the accuracy exceeds 85%, the difficulty is increased by reducing the contrast by 0.1. Once the visual performance (discrimination accuracy) of a training position shows significant improvement and stability for three consecutive sessions, the training position expands radially (by 1 degree) into the surrounding area to enhance the visual training effect. The entire training procedure is automatically controlled by a customized computer program, following the aforementioned rules. The difficulty level for each session is determined based on the participant’s performance in the previous session. To evaluate the effectiveness of the training, the experimenter monitors the participant’s results on a weekly basis.

tES will be administered using a direct current stimulation (tDCS) protocol with a Nurostym tES device (Neuro Device Group SA, Poland). tDCS is a commonly used protocol that may increase the excitability of stimulated cells and affect neuronal resting membrane potentials, thereby altering the local concentration of neurotransmitters [41, 42]. Stimulation is delivered by two 5 cm × 5 cm rubber electrodes placed inside saline-soaked sponges, with the current intensity set to 2 mA, as per previous studies [43, 44]. Participants receive either active anodal tDCS or sham anodal tDCS for 20 min, with 20 s of fade-in and fade-out, depending on their assigned group. The anodal electrode is positioned at Oz (visual cortex), while the cathodal electrode is placed on the cheek. The choice of cheek side is determined by the trained glaucoma eye and the location of the visual field defect to enhance the stimulation effect. For instance, if the left eye is the training eye with a more severe visual defect in the left field, the right cheek will be positioned as the cathodal site. In cases where there is no obvious lateralized injury in the training eye, the contralateral cheek of the training eye will be selected as the cathodal site.

Participants will be randomly assigned to three different groups.Real PL + real tES. In this group, participants will receive 30 training sessions (10-time training × 3 blocks) with real PL and real tES (2 ~ 3 sessions per week, about 1 h per session).Real PL + sham tES. In this group, participants will receive 30 training sessions (10-time training × 3 blocks) with real PL and sham tES (2 ~ 3 sessions per week, about 1 h per session).Placebo PL + sham tES. In this group, participants will receive 30 training sessions (10-time training × 3 blocks) with placebo PL and sham tES (2 ~ 3 sessions per week, about 1 h per session).

### Criteria for discontinuing or modifying allocated interventions {11b}

Given that the procedures in the current study are generally low-risk, the likelihood of participants’ withdrawal or discontinuation is minimal. However, since the majority of our participants are elderly individuals, we will closely monitor and promptly address any discomfort or changes in their health that are unrelated to the study that may affect their participation.

### Strategies to improve adherence to interventions {11c}

To improve study adherence, each participant receives personalized attention from a trained research staff member on the training day and during all assessments. Participants are encouraged to stay focused and approach the entire training procedure with confidence. These measures are designed to promote engagement and commitment to the study interventions.

### Relevant concomitant care permitted or prohibited during the trial {11d}

During recruitment and prior to each treatment session, participants are instructed not to participate in any concurrent interventions throughout the duration of the study. This includes other non-invasive brain stimulation experiments or any forms of physical training. All urgent interventions or treatments that occur will be documented in the research records.

### Provisions for post-trial care {30}

No provision for post-trial care will be provided, as the interventions have been found to be safe. Participants will return to the standard care when the trials conclude. Besides, all enrolled participants will be provided with insurance, which provides compensation for any study-related injuries.

### Outcomes {12}

Participants will have thirty-session trainings, with assessments conducted at six different time points. These assessments consist of a baseline test (T1), a test after completing the first block of training (T2), a test after completing the second block of training (T3), a test after completing all training sessions (T4), a test 1 month after completing all training sessions (T5), and a test 2 months after completing all training sessions (T6). The time points for training and assessment can be seen from Fig. 2. At the baseline, participants’ ocular health will be assessed, including (1) visual acuity (VA): tested monocularly and binocularly using the Early Treatment of Diabetic Retinopathy Study (ETDRS) chart with best-corrected refractive corrections and habitual spectacle corrections; (2) contrast sensitivity (CS): assessed using a MARS Numerical Contrast Sensitivity at 50 cm (with appropriate near addition); and (3) retinal nerve fiber layer thickness (RNFL) using spectralis optical coherence tomography (OCT, Heidelberg Engineering, Heidelberg, Germany). Outcomes that will be repeatedly assessed throughout the entire experiment procedure are shown in Fig. 3.

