### Sample size {14}

The sample size calculation for linear multiple regression with three groups and six time points was performed using G*Power (version 3.1). According to the HRP results from phase 1 study [37] in the GREAT project (Cohen’s *f*^2^ = 0.1), a sample of 144 glaucoma patients will be needed to provide 80% power to detect a significant difference in visual field among three groups at the 2-tailed 0.05 alpha level, assuming a 20% dropout rate.

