## Statistical methods

### Statistical methods for primary and secondary outcomes {20a}

At the conclusion of this project, we will perform statistical analysis based on the intention-to-treat (ITT) principle. For the primary outcome, the differences of MD measured using the 24–2 SITA HFA will serve as an indicator of the effectiveness of interventions. Among the three groups, the intervention group showing the greatest improvement in MD will signify the strongest impact of rehabilitation. Additionally, changes in MD across six time points (baseline, interim 1, interim 2, post-intervention, 1-month post-intervention, and 2-month post-intervention) will reveal the dose-response relationship and recovery duration.

To address inter-individual variability, we will employ a linear mixed model with intervention type and time point as the fixed effect, and baseline MD value as the covariate. A dummy-coding scheme with the placebo PL + sham tES condition as the reference level will be utilized. Initially, a full model will be fitted, and if convergence issues or overfitting arise, adjustments will be made to the random intercept and slope. Model comparison will be conducted using a likelihood-ratio test to evaluate the adequacy of the current model relative to alternative models without the fixed effect. The level of statistical significance for analysis is set at a two-sided *p* < 0.05.

To address the potential attrition and missing data due to participant drop-out, we will conduct sensitivity analyses using multiple imputation methods. Specifically, we will employ the fully conditional specification (FCS) method. This method allows for the imputation of missing data for multiple variables with different distributions. By conducting these sensitivity analyses, we aim to assess the robustness of our primary analysis results to potential attrition bias and missing data. The multiple imputation approach will provide a principled way to handle missing data, ensuring that our conclusions are not unduly influenced by the potential non-random nature of missing data.

The analyses of secondary and exploratory outcomes will follow a similar approach to that of the primary outcome. A detailed statistical analysis plan for secondary and exploratory outcomes is being developed and will be reviewed of by the steering group prior to data analysis.

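### T2 to T6 are timed only by completing training, and the text gives no visit to a participant who stops early, so their intention-to-treat outcome would be filled in although it could be observed

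*Protocol article*

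**What the plan says.** **Visit timing.** Protocol article, Outcomes {12}, defines the interim visits as "a test after completing the first block of training (T2), a test after completing the second block of training (T3"), the next two as "a test after completing all training sessions (T4), a test 1 month after completing all training sessions (T5"), and the last as "a test 2 months after completing all training sessions (T6"). The Primary outcome section places the Humphrey 24-2 test at these same six time points. No time from randomisation is given.

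**Training pace.** Intervention description {11a}: 30 sessions in three blocks of 10, at "2 ~ 3 sessions per week, about 1 h per session".

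**Stopping early.** The section on discontinuing or modifying interventions {11b} offers only the expectation that "withdrawal or discontinuation is minimal" (the words describe the likelihood). It does not separate stopping training from leaving follow-up. The retention section {18b} pays a travel allowance to participants who finish both the training and the assessments.

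**Analysis.** Statistical methods {20a}: "we will perform statistical analysis based on the intention-to-treat (ITT) principle", using a linear mixed model, with multiple imputation as a sensitivity analysis. Section {20c} keeps every randomised participant in the analysis by last value carried forward and makes the per-protocol analysis secondary.

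**Planned loss.** Sample size {14}: 144 participants, "assuming a 20% dropout rate".

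**The concern.** An intention-to-treat comparison asks what happens to MD in everyone assigned to an arm, whether or not they finish 30 sessions. That needs MD measured after the training period in people who stopped. Here the trigger for T4 is the last session, and T5 and T6 count from it. For a stopper the trigger does not occur, and the article names no substitute date. The travel allowance adds a reason not to return.

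An analysis plan cannot repair this later, because it can choose a method for missing values but cannot recover visual field tests that nobody booked. The trial would rely on assumptions about participants who may be willing to attend and whose outcome takes one field test to obtain.

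**Working it through.** **1. The plan's own sample size.** Inputs from {14}: f² = 0.1, power 80%, two-sided alpha 0.05, 20% dropout. The calculation is an F test for multiple regression with noncentrality f² × N. The article does not give the number of tested predictors. With three, N = 114, and 114 / (1 − 0.20) = 142.5, so 143. That agrees closely with 144, or 48 per arm. Two predictors give 100, then 125; four give 125, then 157. So 144 is best read as about 114 evaluable participants inflated for 20% loss.

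**2. How many could be affected.** 144 × 0.20 = 28.8, about 29 in total; 28.8 / 3 = 9.6, about 10 per arm. This counts every planned dropout as someone who stops training but could still be tested.

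**3. Which visits have a trigger, by time of stopping.**
- Stops before session 10: none of T2 to T6.
- Stops in block 2: T2 only.
- Stops in block 3 before session 30: T2 and T3 only.
- Finishes 30 sessions and then leaves: T4, T5 and T6 are all defined, so a missed visit is not due to the anchoring.

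**4. What each stated method does for a stopper.**
- Last value carried forward {20c}: MD is frozen at the last visit. For a block 1 stopper that is baseline, so zero change.
- Mixed model and multiple imputation {20a}: under missing at random, the stopper is projected along the path of participants with similar earlier values who kept training.
- Neither uses the stopper's own post-training MD.

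**5. How far apart these can be (illustration, not from the documents).** Let G be the mean MD gain with full training, p the share who stop, and g the share of G that stoppers retain. The mean over everyone assigned is G × [1 − p(1 − g)]. With p = 0.20:
- g = 0 gives 0.80G; g = 0.5 gives 0.90G; g = 1 gives 1.00G.
- Carrying baseline forward for block 1 stoppers returns 0.80G whatever g is.
- Projecting stoppers as continuers returns about 1.00G whatever g is.

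If g lies between 0 and 1, carry-forward can be too low by up to 0.20G and projection too high by up to 0.20G. If stoppers worsen (g below 0), both are too high. The documents give neither g nor stopping rates by arm, so the direction is open.

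**6. Whether dates can be set for stoppers.** At 3 sessions a week, 30 / 3 = 10 weeks; at 2 a week, 30 / 2 = 15 weeks. Uninterrupted training therefore puts T4 at about week 10 to 15, with T5 and T6 one and two months later. A substitute date can be worked out from the stated pace.

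**The case against.** **The anchoring is deliberate.** Objectives {7} includes finding the optimal dosage, and {20a} reads dose-response and recovery duration from the six visits. T2, T3 and T4 mark 10, 20 and 30 sessions. Re-dating all visits from randomisation would mix doses among people training at different paces. This stands, and it is why the change should apply only to participants who stop.

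**The article condenses a fuller protocol.** Section {31c} refers to a full protocol, and the visit figures and timeline table are not shown. No sentence says assessment ends when training ends. A reader might infer that a stopper can never reach T4 to T6, but that goes beyond the text. What the text supports is narrower: the visit definitions it does give exclude stoppers, and the sections on discontinuation, retention and missing data, where an exception would belong, contain none.

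**All randomised participants are kept.** A reader might infer that the analysis is in effect restricted to completers. Section {20c} rules that out by carrying values forward for everyone and making the per-protocol analysis secondary. Nor is it wholly an as-if-trained analysis, since that describes the model and imputation but not carry-forward.

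**Expecting few withdrawals while allowing for 20% loss is ordinary planning.** Agreed. The difference between {11b} and {14} is not itself a fault.

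**Conclusion.** The point holds in a limited form. As written, the plan gives no post-training test to participants who stop early, and under a stated intention-to-treat principle it would fill in an outcome that could be observed.

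The size is at most about 29 of 144 participants, about 10 per arm. The true number is lower to the extent that the planned 20% includes people who withdraw completely, whom no visit rule recovers, or people who finish training and then miss T5 or T6.

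A reader might go on to infer that the treatment effect is overstated by 25% (1 / 0.8 − 1). That figure compares a completer-only mean with a population in which stoppers keep no gain. It does not describe carry-forward, which gives 0.80G for block 1 stoppers under the same assumption. A reader might also expect a shift between arms from unequal stopping. The documents give no stopping rates by arm, and all three arms have the same number and pace of sessions under blinding, so no figure can be put on it.

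This conclusion rests on the article's text alone. If the full protocol already schedules tests for participants who stop, the remedy is to say so in the Outcomes section.

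**What to change.** Leave T2 to T6 anchored to training for participants who continue. Add to Outcomes {12}:

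- A participant who stops training is still assessed, at least with the Humphrey 24-2 test at T4, T5 and T6, on the dates those visits would have fallen at the planned session pace, unless consent for follow-up is withdrawn. Because the pace is a range, name one date rule, the same in every arm, such as the session calendar booked at the start.
- The number of sessions received is recorded at each visit, so that dose-response uses the actual dose.

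In {20a} and {20c}, state that these observed values enter the intention-to-treat analysis. In {18b}, do not make the allowance for assessment visits depend on completing training.

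**Cost.** A wording amendment, a visit-calendar change, and a few visits for people no longer training; no new procedure. The intention-to-treat estimate may be smaller. As an illustration with three tested predictors, f² = 0.1 scaled by the squared attenuation, and all 20% being stoppers, testing all 144 gives power 0.71, 0.82 or 0.90 if stoppers keep none, half or all of the effect. The 115 who finish would give 0.81, but for the effect in people who complete training, which is a different question.

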**Fig. 2 Fig2:**
[figure not shown]
The six time points for the 30-session trainings (PL + tES) and the assessments

**Fig. 3 Fig3:**
[figure not shown]
Assessment overview: this figure provides a comprehensive view of all assessments conducted during the current clinical trial and the time points of each assessment

#### Primary outcome

Visual field test is measured monocularly using the 24–2 and 10–2 Swedish interactive threshold algorithm (SITA) standard tests by Humphrey visual field analyzer (HFA, Carl Zeiss Meditec Inc., California). The mean deviation (MD), pattern standard deviation (PSD), and visual field index (VFI) are recorded and the MD of 24–2 visual field test is used as primary outcome of intervention effectiveness. HFA visual field test is conducted at six time points, from T1 to T6.

#### Secondary outcomes

HRPThe current HRP is a valid and reliable computer-based visual field assessment based upon a previously well-established program [45]. The revised HRP uses circular geometry instead of a rectangle to present stimuli, while maintaining its high-resolution advantage. During the HRP test, suprathreshold stimuli are presented in a radial pattern within 20 degrees, with a step size of 3 degrees. These stimuli are presented monocularly at a total of 98 positions, with the order of presentation randomized. To ensure a stable result and accurate assessment of participants’ responses, the HRP test is repeated five times. Throughout the HRP test, fixation is monitored by an infrared eye tracker (SR Research, Eyelink Portable Duo). HRP testing is conducted at six time points, from T1 to T6.

2)Electroencephalography (EEG)EEG is used to reveal the pathological and neural mechanisms of intervention. Three task-related EEG experiments are designed to detect changes in integrated and peripheral visual function brought by the training. Additionally, the resting state EEG is recorded to reveal any changes in functional connectivity changes induced by training. A high-resolution 64-channel Quik-Cap Neo Net from Compumedics Neuroscan, in conjunction with a SynAmps amplifier, will be employed for EEG recording. During the process, the impedance from all channels will be maintained below 10 kΩ.

The ISCEV standard visual evoked potentials (VEP) protocol serves as the first EEG task [46]. A 1 Hz (500 ms in each phase) pattern reversal checkerboard is presented to the full visual field, and participants are asked to fixate on a red central point to maintain fixation. To improve the repeatability, the stimuli will be presented in two blocks of 34 s (68 reversals per block). The sequence of recordings is left eye first, followed by the right eye, and then both eyes during each EEG visit. The event-related potential (ERP) components derived from the task, such as the peak amplitude, peak latency, and peak latency/amplitude of N75, P100, and N135, will be analyzed.

The second task involves a 6 Hz steady-state visual evoked potential experiment (SSVEP) with each block lasting 20 s and a total of 3 blocks. Compared to VEP, the SSVEP has a higher signal-to-noise ratio (SNR) and may be more suitable for detecting changes in participants with severe glaucoma. A Fourier transformation will be used to extract the 6 Hz induced amplitude response. Additionally, the averaging method of neighborhood frequencies will be used to calculate the SNR.

The third task involves a modified version of radial flashed SSVEP. Instead of using the traditional rectangle reversal checkerboard, this design incorporates 5 differently sized embedded rings. The dartboard design is based on multifocal visual evoked potential (mfVEP) stimulus design [47]. In the experiment, the rings will flash at a frequency of 6 Hz in random order to elicit peripheral responses. Each ring will flash for three blocks, with each block lasting 20 s. Consequently, the induced amplitude and SNR at 6 Hz will be calculated as the measures of intervention.

For the resting-state EEG, 3-min closed eye and 3-min open eye will be recorded. To increase participants’ compliance, soft music of a same sound track is played during the resting state recording at each visit. During the eyes-open recording, participants are asked to fixate a physical hourglass to help minimize eye movement [48]. Measures of the intervention effect will include peak alpha, spectrum power, and functional connectivity network. EEG tests are conducted at four time points—T1, T4 to T6 (refer to Table 2 for details).

3)Balance and gait testsPatients with visual field loss reported a higher risk of falling compared with those with normal vision [49] and balance and gait performance are significant factors in falls among glaucoma patients [50]. Therefore, improving balance and/or gait performance can be an important predictor of QoL improvement and safety among patients with glaucoma.

Gait test (Fig. 4)

